### Rationale and Aims

#### Overall Aim

The overall aim is to further clarify and operationalize the interrelated concepts of playfulness and playful activities among older adults receiving municipal care and to develop an instrument suitable for psychometric testing.

#### Phase 1—Conceptual Exploration

The overall aim of phase 1 is to deepen understanding of playfulness among older adults living in long-term care facilities. This includes exploring their lived experiences, engagement in playful activities, and the perspectives of care staff. A further objective is to examine how playfulness relates to well-being in this population.

Specific objectives are as follows:

To describe playfulness as experienced by older adults living in long-term care facilitiesTo explore older adults’ experiences of engaging in playful activities and their relation to health and well-beingTo investigate activity coordinators’ and managers’ experiences of older adults’ possibilities and barriers to express their playfulnessTo develop a first version of the PLAY-SE instrument, including initial item generation and pilot testing to explore its measurement properties and guide further refinement

#### Phase 2—Instrument Development and Psychometric Evaluation

The overall aim of phase 2 is to advance the development of the PLAY-SE instrument by exploring its theoretically developed domains against empirical data, refining its conceptual structure, and strengthening content validity [36]. This phase will also involve systematic psychometric evaluation, including assessments of usability, reliability, dimensionality, and validity, to ensure that the instrument provides a robust and nuanced measure of playfulness among older adults in the context of illness or institutional care.

Specific objectives are as follows:

To strengthen the theoretical and conceptual basis for the instrumentTo assess content validity and usability through interviewsTo conduct an initial psychometric evaluationTo validate a revised version using a larger, representative sample

This phase will also examine associations with the SMAP [25] and indicators of well-being among older adults receiving municipal care and service support.

## Methods

### Overall Design

Inspired by Huber et al [45] and the “hybrid model of concept development” [46], this program applies a hybrid model of concept development combined with an embedded mixed methods design. The hybrid model is particularly suited for refining and clarifying complex concepts by integrating theoretical insights with empirical observations. Concept development enhances conceptual clarity by identifying the essential attributes of a construct and translating them into measurable dimensions.

The hybrid model unfolds in 3 interrelated cycles (Figure 1):

Theoretical cycle: A literature review is conducted to examine how the concept has been defined and measured previously. In this protocol, this cycle has been initiated through a structured exploratory literature review using the Elicit platform and a synthesis of prior studies (see Literature Review). These findings inform conceptual clarifications of play and playfulness (see Conceptual Clarifications), tailored to the study’s aims.Fieldwork cycle: Empirical data are collected and analyzed to investigate how the concept is expressed in real-world contexts. In phase 1, phenomenological interviews with older adults in municipal care provide meaning units that expand, refine, or challenge the preliminary theoretical understanding.Analytical cycle: Empirical findings are reintegrated with the theoretical groundwork to develop a refined conceptual description. This refined description directly informs item generation and domain structure for the PLAY-SE instrument in phase 2. Thus, qualitative findings are systematically translated into candidate items, which are subsequently evaluated and refined through cognitive interviews and psychometric testing.

The cycles are applied iteratively, meaning that quantitative findings from pilot testing and Rasch analysis may prompt further conceptual reflection to ensure alignment between empirical performance and theoretical meaning. Together, these cycles underpin the 2 phases of the PLAY-SE program: phase 1 (conceptual exploration) and phase 2 (instrument development and psychometric evaluation).

### Setting and Participants

The program will be conducted in residential care facilities (ie, nursing homes) and in ordinary housing among persons receiving municipal care support in Sweden. Participants will include older adults aged 65 years and older, as well as activity coordinators and managers involved in municipal elder care.

Inclusion criteria (phase 1 and phase 2) were as follows:

Older adults aged 65 years or olderReceiving municipal care support, either in residential care facilities or in their own homesAble to provide informed consentSufficient cognitive and communicative ability to participate in interviews, surveys, or focus groups

Exclusion criteria (phase 1 and phase 2) were as follows:

Severe cognitive impairment or acute illness that prevents informed consent or meaningful participationNon-Swedish–speaking persons (due to the instrument being developed and tested in Swedish)

Preliminary sample size of phase 1 (conceptual exploration) was as follows:

Approximately 15 to 25 older adults for qualitative interviews and 10 to 15 activity coordinators or managers for focus groups (guided by data saturation).

Preliminary sample size of phase 2 (instrument development and psychometric evaluation) was as follows:

Content validity interviews with 10 to 15 older adults and 6 to 10 experts.A pilot survey including approximately 100 older adults to test the PLAY-SE instrument, version 1, and explore its initial measurement properties, as well as associations with SMAP [25] and well-being indicators.Large-scale validation study including 250 to 500 older adults to confirm psychometric properties (CTT and modern test theory).

### Sampling Strategy

A purposive sampling strategy will be used in phase 1 to ensure variation in gender, age, and relevant care contexts within municipal elder care. The aim is not statistical representativeness but conceptual variation to inform domain development, with particular emphasis on older adults living in residential care facilities.

For phase 2 (psychometric testing), a stratified sampling approach will be applied across multiple participating municipalities, including both urban and rural contexts. Recruitment will focus primarily on older adults receiving municipal care support in ordinary housing while ensuring sufficient variation in demographic and contextual characteristics. Eligible individuals will be invited consecutively or through structured random selection, where feasible. This approach aims to enhance representativeness within the intended target population while acknowledging practical constraints within municipal services.

To reduce recruitment bias, initial contact will be facilitated by designated care staff, but final eligibility confirmation and informed consent will be handled directly by the research team. Recruitment procedures will be documented to allow transparent reporting of participation rates and sample characteristics.

### Sample Size Considerations

The planned sample sizes are based on methodological considerations specific to qualitative research, CTT, and RMT.

For the qualitative interviews in phase 1 (approximately 15‐25 older adults), the sample size is guided by the principle of conceptual saturation and information power, where the aim is depth and variation rather than statistical representativeness [32]. Recruitment will continue until thematic depth and conceptual clarity are achieved across variations in gender, care setting, and functional status.

For pilot testing (approximately 100 participants), the sample size is considered sufficient for preliminary evaluation under CTT, including the assessment of internal consistency, item-total correlations, floor and ceiling effects, and exploratory dimensionality [37,38,47]. Samples of around 100 participants are commonly recommended for early-stage scale refinement to identify poorly functioning items and evaluate reliability coefficients such as Cronbach α [38].

For large-scale validation (250‐500 participants), the sample size is aligned with recommendations for RMT. Samples of approximately 250 participants allow reasonably stable estimation of item difficulty parameters, while samples approaching 500 participants improve the precision of item calibration and enable robust testing of differential item functioning (DIF) across subgroups [48-50]. Larger samples also strengthen the evaluation of unidimensionality and local independence and support more precise targeting of the instrument [51].

Together, these staged sample sizes are intended to ensure conceptual validity in phase 1 and rigorous psychometric evaluation in phase 2, in line with best practice recommendations for scale development.

### Recruitment Procedures

Participants will be recruited from both residential care facilities and ordinary housing with municipal home care support. Recruitment procedures will be adapted to each setting while maintaining consistent inclusion criteria. In residential care, responsible nurses or care managers will identify potentially eligible participants based on documented eligibility criteria and provide initial study information. In home care settings, recruitment will occur through designated contact persons within municipal services who distribute study information to eligible individuals. In all settings, final eligibility and informed consent will be confirmed directly by the research team to ensure voluntariness and comprehension.

### Assessment of Cognitive Ability

Eligibility requires sufficient cognitive and communicative capacity to understand study information and provide informed consent. Formal cognitive screening instruments will not be administered as part of the study. Instead, the assessment of cognitive capacity will be based on structured clinical judgment conducted in collaboration with responsible nurses or care staff, drawing on documented cognitive status in medical records and their ongoing knowledge of the individual’s functioning.

The assessment will focus on the participant’s ability to do the following:

Understand the purpose of the studyComprehend what participation entailsExpress a voluntary decision regarding participation

If uncertainty arises regarding decisional capacity, the individual will not be included. The basis for inclusion decisions will be documented to ensure procedural consistency.

### Administration Procedures and Mode Effects

The PLAY-SE instrument is designed for self-administration. However, given the target population, some participants may require assistance (eg, due to visual impairment or motor limitations). To ensure procedural consistency, assistance will follow a standardized protocol. Support will be limited to reading items aloud and recording responses as expressed by the participant, without interpretation, rephrasing, or prompting. The mode of administration (independent completion vs assisted completion) will be documented for each participant. This variable will be included in subsequent psychometric analyses.

Potential mode effects will be examined analytically. In the Rasch analysis, DIF will be tested across administration modes to determine whether assisted completion systematically influences item responses. If significant DIF is identified, its impact on measurement invariance will be evaluated.

### Item Generation and Content Development

Initial item development will be informed by the theoretical framework and the structured literature review described in this protocol, as well as by the research team’s clinical and methodological expertise within gerontological care [52]. In addition, qualitative findings from phase 1 will contribute empirical grounding through a structured process in which meaning units are identified, clustered into conceptual domains, and translated into candidate items.

While older adults’ lived experiences provide the empirical foundation for item content, item generation will not rely solely on participants’ verbatim expressions. In line with the notion of epistemic dialogue in patient-centered measurement [52], experiential knowledge will be treated as a vital but not self-sufficient source of evidence. Participants’ perspectives will inform item content and relevance, yet they will also be examined, conceptually refined, and integrated with theoretical frameworks (eg, person-centered care and lifeworld theory) and psychometric principles. In this way, the research team plays an active role in ensuring that items reflect both lived experience and a coherent construct suitable for rigorous measurement.

For each domain, an initial item pool (approximately 3‐5 items per domain) will be generated to capture varying levels of endorsement along the hypothesized continuum from lower to higher expressions of playfulness. Items will be formulated in Swedish using clear, concrete, and contextually appropriate language.

Item wording and content will be reviewed in 3 stages:

Internal expert review focusing on conceptual coherence and redundancyCognitive interviews with older adults to assess clarity, relevance, and interpretabilityIterative refinement based on empirical feedback and measurement considerations

All decisions regarding item inclusion, modification, or exclusion will be documented to ensure transparency.

### Documentation of Item Decisions

All stages of item development will be documented to ensure transparency and reproducibility. A structured decision log will be maintained throughout the development process, recording the origin of each item (eg, qualitative finding, theoretical refinement, or expert suggestion), revisions to wording, and the rationale for retention, modification, or exclusion.

During pilot testing and initial CTT analyses, the item pool will be retained in its entirety to preserve conceptual breadth. Early item removal will be avoided unless an item demonstrates clear redundancy or fundamental comprehension problems.

Subsequent Rasch analysis will provide a more rigorous evaluation of dimensionality, threshold functioning, item fit, and DIF. Decisions regarding item removal will be based on an integrated assessment of statistical performance and conceptual relevance. Items will not be removed solely on the basis of misfit statistics; instead, conceptual coverage, theoretical coherence, and construct validity will be weighed alongside empirical indicators.

This staged approach ensures that item reduction, if necessary, occurs only after a comprehensive psychometric evaluation and is supported by both measurement and conceptual considerations. The full decision process will be documented to provide a transparent audit trail linking qualitative findings, theoretical assumptions, and psychometric analyses to the final item selection.

### Prespecified Psychometric Criteria

Prespecified psychometric criteria have been defined to guide the evaluation and scale refinement of PLAY-SE. These criteria, grounded in established methodological literature, specify statistical thresholds and decision rules under both CTT and RMT (Table 2).

**Table 2. T2:** Prespecified criteria for psychometric evaluation and scale refinement of the Play and Supportive Environments instrument.

Measurement property	Method	Criterion	Decision rule	Reference
Content validity	I-CVI^a^	≥0.78	Item revised if <0.78	[53]
Content validity	S-CVI^b^	≥0.90	Overall revision if <0.90	[53]
Data quality	Missing data per item	<10%	Investigate content, wording, and administration if ≥10%	[47]
Floor/ceiling effects	% lowest/highest category	≤20%	Consider revision if >20%	[47]
Internal consistency (CTT)^c^	Cronbach α	≥0.70 (group level)	Review scale if <0.70	[47]
Item-total correlation (CTT)	Corrected item-total	≥0.30	Review if <0.30	[47]
Dimensionality (CTT)	EFA loadings	≥0.40 on intended factor	Review cross-loading items	[38]
Rasch model fit (RMT)^d^	Item fit residual	−2.5 to +2.5	Review outside range	[54]
Threshold ordering (RMT)	Category probability curves	Ordered thresholds	Consider collapsing categories if disordered	[51,54]
Local independence (RMT)	Residual correlations (Yen Q3)^e^	<0.20 above average	Consider subtests or revision	[54,55]
Reliability (RMT)	PSI^f^	≥0.70	Review if <0.70	[54]
DIF^g^ (RMT)	2-way ANOVA on residuals	Nonsignificant after Bonferroni adjustment^h^	If significant, consider item split	[54,56]
Unidimensionality (RMT)	PCA^i^ of residuals + *t* tests	≤5% significant	If >5%, explore substructure	[51,57,58]
Item removal principle	Integrated conceptual + statistical evaluation	Not solely data driven	Remove only after Rasch and conceptual review	[36,52]

a I-CVI: Item Content Validity Index.

b S-CVI: Scale Content Validity Index.

c CTT: classical test theory.

d RMT: Rasch measurement theory.

e Yen Q3: residual correlation index used to assess local dependence in Rasch analysis.

f PSI: Person Separation Index.

g DIF: differential item functioning.

h Bonferroni adjustment refers to correction for multiple testing by dividing the significance level by the number of comparisons.

i principal component analysis

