Taken together, qualitative studies highlighting meaning, continuity, and connectedness [8,9,20,21] and quantitative research linking playfulness with well-being [2,3,23] suggest that playfulness in older age is complex, contextual, and relational. However, existing instruments primarily conceptualize playfulness as a personality trait and have been developed for general adult populations. They place less emphasis on how playfulness is enacted in everyday life within care contexts or on how environmental and functional constraints may shape this expression.

Valid and age-sensitive instruments, responsive to functional limitations and municipal care environments, are therefore needed to capture these nuances in both research and practice. PLAY-SE will be grounded in older adults’ lived experiences within Swedish municipal care and will integrate perspectives from caring science and person-centered care. It will be developed with explicit Rasch-based psychometric intentions to ensure appropriate targeting and invariant measurement in this specific population. For these reasons, adaptation of existing instruments was considered insufficient to meet the conceptual and methodological aims of this research program.

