### Initial Conceptualization and Theoretical Hierarchy

As part of this review and study protocol, an initial conceptualization and theoretical hierarchy for the PLAY-SE instrument were developed. This process drew on insights from the literature, together with conceptual reasoning, providing a theoretically grounded basis for the forthcoming item generation and psychometric evaluation. The conceptualization and hierarchy will be further elaborated in forthcoming discussions within the research team, drawing on findings from phase 1 and serving as a springboard for phase 2 of the program. The PLAY-SE will be a self-administered instrument comprising approximately 25 statements across 6 preliminary conceptual domains: : “Across the Life Course,” “Attitudes,” “Environment and Enablers,” “Emotional Meaning,” “Health and Well-being,” and “Playful Activity.” While designed for independent completion, support from staff should be offered, if needed, to ensure that all participants can engage with the instrument on their own terms. Higher scores will reflect greater levels of playfulness or engagement in play among older adults receiving municipal care (Figure 2).

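### The DIF criterion rests on a nonsignificant Bonferroni-adjusted test with no bound on DIF size, and applies unchanged at N=250 although robust DIF testing is tied to samples near 500

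*Protocol article*

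**What the plan says.** Prespecified Psychometric Criteria, Table 2, tests DIF by "2-way ANOVA on residuals". The criterion is "Nonsignificant after Bonferroni adjustment" and the decision rule is "If significant, consider item split". The table footnote explains the adjustment as "dividing the significance level by the number of comparisons", but gives neither the number of comparisons nor the starting significance level.

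Administration Procedures and Mode Effects applies DIF testing to independent versus assisted completion. The effect on invariance is to be evaluated when significant DIF is found; nothing is specified for a nonsignificant result.

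Setting and Participants allows 250 to 500 people in the validation study. Sample Size Considerations justifies about 250 by the stability of item difficulty estimates, "while samples approaching 500 participants improve the precision of item calibration and enable robust testing of differential item functioning (DIF) across subgroups". No minimum subgroup size is given.

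The end of Literature Review says that PLAY-SE is built on Rasch principles "to ensure appropriate targeting and invariant measurement in this specific population", as part of the argument for a new instrument over adapting an existing one.

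**The concern.** A nonsignificant test shows that DIF was not detected. It does not show that DIF is small. When nonsignificance is the criterion, anything that weakens the test helps the instrument to pass: fewer participants, a thin subgroup, or a larger Bonferroni divisor. This follows from the form of the rule and needs no assumed inputs. Several other rows of Table 2 (alpha, Person Separation Index, factor loadings, residual correlations) set limits on magnitude; the DIF row does not.

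The protocol itself separates what 250 supports from what about 500 supports, but does not carry that distinction into Table 2. A study that closes at 250 is judged by the same rule as one that reaches 500.

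Two conclusions are at stake. One is invariant measurement, part of the case for a new scale. The other is that assisted completion does not distort responses; Ethical Considerations relies on the same DIF test to address social desirability bias. Assisted completers may well be a minority, since the protocol expects some participants to need help and recruits mainly from ordinary housing.

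**Working it through.** **No figure to reproduce.** The protocol gives no DIF power, DIF size of interest or alpha, so 250 to 500 cannot be reproduced as a DIF sample size.

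**Inputs from the protocol.** N is 250 to 500. The instrument is described as "comprising approximately 25 statements across 6 preliminary conceptual domains"; the pool of 6 domains with 3 to 5 items each gives 18 to 30. The test is a two-way ANOVA on residuals with Bonferroni adjustment.

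**Inputs assumed, because they are not stated.**
- One item with uniform DIF of 0.5 logit.
- Two-sided alpha of 0.05 before adjustment, with k=25 tests (one per item) or k=50 (group effect plus interaction). The per-test level is 0.05/25 = 0.002 or 0.05/50 = 0.001, with critical values 3.090 and 3.291.
- Two, four, five or seven response categories. Thresholds are evenly spaced over ±1.0 (four), ±1.5 (five) and ±2.0 logits (seven); the close-threshold case is five categories over ±0.75.
- Person SD 1.0 or 1.5 logits.
- Smaller group f = 50%, 20% or 10% of N.

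**Normal approximation.** With I the mean Rasch item information per person,

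SE = √[(1/I) × (1/(Nf) + 1/(N(1−f)))], power ≈ Φ(0.5/SE − critical value).

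Five categories, person SD 1.0, I = 0.79, N = 250:
- 50:50: SE = √[(1/0.79)(1/125 + 1/125)] = 0.142. Power = Φ(3.51 − 3.09) = 0.66 at k=25 and Φ(3.51 − 3.29) = 0.59 at k=50.
- 20:80: SE = √[(1/0.79)(1/50 + 1/200)] = 0.178. Power = 0.39 and 0.32.
- 10:90: SE = √[(1/0.79)(1/25 + 1/225)] = 0.237. Power = 0.16 and 0.12.

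Smallest DIF detectable with 80% power at 50:50: (3.090 + 0.842) × 0.142 = 0.56 logit, or 0.59 at k=50. At 20:80 it is 0.70 to 0.73.

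**Simulation of the planned test** (25 items, residual ANOVA of group by five class intervals, 250 replicates, or 600 for dichotomous items). Power for 0.5 logit, k=25 / k=50:

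| Items | N=250, 50:50 | N=250, 20:80 | N=500, 50:50 |
|---|---|---|---|
| Five categories, SD 1.0 | 0.58 / 0.51 | 0.31 / 0.24 | 0.96 / 0.94 |
| Five categories, SD 1.5 | 0.46 / 0.40 | 0.25 / 0.17 | 0.92 / 0.88 |
| Four categories, SD 1.0 | 0.44 / 0.36 | 0.22 / 0.15 | 0.92 / 0.87 |
| Dichotomous, SD 1.0 | 0.07 / 0.05 | 0.03 / 0.01 | 0.27 / 0.22 |

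Without Bonferroni, the five-category, SD 1.0, 50:50 figure at N=250 is 0.89, so the adjustment alone brings it down to 0.58 or 0.51.

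**Favourable cases** (approximation, N=250, k=25 / k=50). Five categories with close thresholds: 0.80 / 0.74 at 50:50 and 0.52 / 0.44 at 20:80. Seven categories: 0.86 / 0.81 and 0.60 / 0.52.

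**Balance still matters at 500.** By the approximation, five categories with SD 1.0 give 0.81 / 0.75 at 20:80 and 0.46 / 0.38 at 10:90.

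**What an interval can show at N=250** (five categories, SD 1.0). The 95% half-width is 1.96 × SE: 0.28 logit at 50:50, 0.35 at 20:80 and 0.46 at 10:90. Against an illustrative ±0.5-logit margin, an item with no DIF would have an interval crossing the margin about 12%, 39% and 88% of the time, or about 3, 10 and 22 of 25 items.

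**The case against.** The protocol never says that a nonsignificant result establishes invariance. Its criteria are there to guide evaluation, and the Discussion leaves the instrument's adequacy to empirical performance in diverse samples. A reader might infer that invariance will be declared on nonsignificance; the text does not go that far. What stands is that nonsignificance is the only stated way to meet the criterion, and nothing further is required once it is met.

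A reader might also infer that the test usually misses a half-logit DIF at 250, or that small samples pass by default. The documents do not support either. The response format, group split, alpha, divisor and DIF size of interest are all unstated. With five categories, SD 1.0 and equal groups the simulated test detects 0.5 logit slightly more often than not, and seven categories or close thresholds bring power to 0.74 to 0.86. DIF somewhat above half a logit would be found with good power in a balanced five-category sample of 250.

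Finally, Sample Size Considerations does not claim robust DIF testing at 250. That is fair, and it narrows the defect to a distinction drawn in one section and not carried into the decision rule. The protocol's integrated conceptual and statistical review does not repair this, because it governs item removal and not DIF that was never flagged.

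**Conclusion.** The concern holds in this limited form. The DIF criterion has no magnitude bound, is easier to meet with less information, and applies unchanged at a sample size below the one that the protocol associates with robust DIF testing. Those statements rest on the text alone.

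The size depends on the assumptions listed above. For 0.5-logit DIF at N=250 over 25 to 50 tests, power is roughly 5% to 65% at 50:50 and 1% to 39% at 20:80 with two to five ordinary categories, and about 74% to 86% at 50:50 in the favourable cases. Even those favourable cases give only 44% to 60% at 20:80, so the weakness is greatest for unbalanced factors such as assisted completion. The percentages show how far the answer moves with unstated inputs; they are not a forecast for this study. The change should be made before the validation study.

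**What to change.** Keep the Bonferroni-adjusted ANOVA as a screen and add to the DIF row of Table 2:
- For every item and factor, report the between-group difference in item location in logits with a 95% CI, judged against a DIF size of concern that the team sets and justifies in advance. The 0.5 logit used here is only illustrative.
- Report how far person measures change when DIF is resolved.
- State that a nonsignificant result with a wide interval is inconclusive and is not evidence of invariance.
- State the starting alpha and the number of comparisons in the Bonferroni divisor.

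In Table 2 and Sample Size Considerations, say that DIF conclusions, including those on administration mode, are exploratory when the achieved N is well below 500 or a subgroup is small. The team should define small from the interval width that it can accept.

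The cost is wording, some extra analysis and a more qualified claim; no more participants are needed. The downside is that some items, and many in thin subgroups, will be reported as inconclusive.

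### Table 2's unidimensionality cut of 5% equals the share expected by chance, so a truly one-dimensional PLAY-SE would often be flagged for substructure

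*Protocol article*

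**What the plan says.** Under Prespecified Psychometric Criteria, Table 2 is introduced as a set of thresholds and decision rules fixed beforehand for both measurement frameworks. In its unidimensionality row:

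- the method is "PCA^i^ of residuals + *t* tests";
- the criterion is "≤5% significant";
- the decision rule is "If >5%, explore substructure".

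The row gives no level for the t tests, no interval or tolerance around the observed share, and no rule for turning PCA loadings into two item sets. The DIF row of the same table does guard against chance findings, through a Bonferroni adjustment. The last row allows item removal only after both Rasch analysis and conceptual review.

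The validation sample is 250 to 500 older adults (Setting and Participants). The instrument is to have "approximately 25 statements across 6 preliminary conceptual domains". Sample Size Considerations adds: "Larger samples also strengthen the evaluation of unidimensionality and local independence".

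**The concern.** In this method each person gets two estimates, one from each item set, and a t test compares them. At a 5% test level, about one person in twenty differs significantly even when both sets measure exactly the same trait. A cut of 5% on the observed share therefore sits at the null expectation, and a sound scale falls on the wrong side of it by sampling variation alone.

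The sets are also chosen by PCA of the residuals in the same data. Depending on how the loadings are used, this selects the contrast that looks most different by chance and raises the null share above 5%.

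PLAY-SE places six domains on one ruler, and this row tests that claim directly. If a one-dimensional scale often trips the rule, a trip says little. The team would then have to split a valid scale or set aside its own criterion after seeing the data.

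**Working it through.** The article states no error rate for this rule, so there is no figure to reproduce.

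**Step 1. Binomial benchmark.** Inputs: cut of 5% (Table 2) and n from 250 to 500 (Setting and Participants). Assumptions: two-sided t tests at 5%, true share exactly 5%, tests independent between persons. With X ~ Binomial(n, 0.05), the false-flag probability is P(X > 0.05n).

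| n | 0.05n | Count that trips the rule | P(trip) |
|---|---|---|---|
| 250 | 12.5 | 13 or more | 0.482 |
| 300 | 15 | 16 or more | 0.432 |
| 400 | 20 | 21 or more | 0.441 |
| 500 | 25 | 26 or more | 0.447 |

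These sizes give 43-48%. Because the count is discrete, the figure moves a little between them; at n=259 (0.05n = 12.95, so 13 or more trips) it is 0.534.

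The result is sensitive to the true share. At n=250 and 500, P(trip) is 0.21 and 0.11 if the true share is 4%, and 0.74 and 0.80 if it is 6%.

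**Step 2. Effect of choosing the sets by PCA.** Truly unidimensional rating-scale Rasch data were simulated. Assumed settings, not document values: 25 items, 5 categories, person SD 1.2 logits, item difficulties from -1.5 to +1.5, weighted likelihood person estimates, cut-off |t| > 1.96, known item parameters.

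| Item sets | n=250: mean share, P(>5%) | n=500: mean share, P(>5%) |
|---|---|---|
| Random halves (no selection) | 4.2%, 0.25 | 4.3%, 0.22 |
| Loadings beyond ±0.3 on the first residual component | 5.7%, 0.64 | 4.1%, 0.17 |
| All items, split by sign of the loading | 8.7%, 1.00 | 7.1%, 0.99 |

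The ±0.3 split reverted to the sign split when either side had fewer than two items. There were 300 replicates per cell at n=250 and 100 at n=500.

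Variants (18 items, 4 categories, or a wider and higher person distribution; 80 to 100 replicates) gave 0.29-0.54 at n=250 and 0.14-0.23 at n=500 for the ±0.3 split, and 0.93-1.00 at n=250 for the sign split. With item parameters estimated from the data (only 20 to 30 replicates), the ±0.3 split gave 0.83 at n=250 and 0.50 at n=500, and the sign split gave 1.00 at both.

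**Step 3. Adding an exact interval.** Flag only if the lower Clopper-Pearson 95% limit exceeds 5%.

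| n | Count needed | P(flag), true share 5% | P(flag), null share 7% | P(flag), null share 8% |
|---|---|---|---|---|
| 250 | 21 (8.4%) | 0.015 | 0.22 | 0.44 |
| 500 | 36 (7.2%) | 0.020 | 0.46 | 0.77 |

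The interval removes the sampling-error problem when the null share is 5%. It does not remove the selection effect when PCA lifts the null share to 7-8%, as the sign split does here.

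**The case against.** The strongest reply is that this is a soft trigger. Exceeding 5% prompts a further look at structure, and no item goes without conceptual review. A reader might infer that the rule rejects a unidimensional scale, but the article does not say so. The cost of a false flag is an extra, documented analysis. This stands, and it lowers the severity.

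A second reply is that no single false-flag rate can be quoted. A reader might infer that a sound scale fails about half the time or more, or almost always. Neither holds generally: the rate is 22-25% with no selection, 14-64% with a ±0.3 split and known item parameters, and close to 100% only with the all-item sign split. The row does not say which split applies. This stands too, although an undefined split is part of what makes the rule hard to interpret.

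A third reply concerns sample size. A reader might infer that larger samples never help and that the sentence in Sample Size Considerations is wrong. On the binomial benchmark the rate hardly moves with n, but with the ±0.3 split it falls from 64% to 17%. That sentence is not shown to be wrong.

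Finally, a journal article can leave the test level and the split rule to a fuller plan. That excuses missing detail. It does not excuse the bare 5% cut, which the article states as its decision rule.

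**Conclusion.** The point holds, at moderate severity. The stated cut equals the chance expectation of a 5% test and allows neither for sampling error nor for data-driven choice of item sets. If the true share is 5%, a unidimensional scale is falsely flagged in about 43-48% of samples at the sizes tabulated between 250 and 500. Under the simulated settings the rate runs from below 20% to nearly 100%, depending on how the sets are formed.

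The benchmark assumes a 5% t-test level and independent tests. The simulation rests on assumed item and person distributions, and its estimated-parameter results come from few replicates. What is damaged is the information value of a prespecified criterion; the documents do not imply automatic loss of the single scale.

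**What to change.** Rewrite the one row of Table 2:

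1. State the t-test level and the exact rule by which PCA loadings form the two item sets. Keep PCA-chosen sets, so that an unanticipated dimension can still be found.
2. Flag only if the observed share exceeds the 95th percentile of shares from data simulated under the fitted Rasch model, with the same n, items and split rule.
3. At minimum, flag only if the lower exact binomial 95% limit exceeds 5% (21 or more of 250; 36 or more of 500), and note that the interval alone does not fully correct for PCA selection with a sign split.

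A split by domain fixed in advance can be added as a supplementary test but should not replace the PCA check. In simulation (150 replicates, assumed settings, the cut-offs in item 3), a fixed split flagged a second trait aligned with it in 100% of datasets. It flagged only about 1% when a second trait correlated 0.5 with the first cut across it.

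The cost is one table row, a short simulation and slightly lower sensitivity to weak multidimensionality. No new data are needed, and large-scale validation is not planned until 2027 to 2029.
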